### Treatment

#### Personalized lifestyle advice

Based on diary observations during the observation month (i.e., three measures per day during 30 days) candidates will receive personalized lifestyle advice. The focus will be on lifestyle behaviors that can potentially be influenced (for exact questions, see Table 2), such as physical activities, diet, sleep, smoking and/or alcohol use, and social contacts. The advice will consist of three main parts. In the first descriptive part of the advice, general information will be presented about the participant’s average levels of lifestyle behaviors and pleasure during the observation month. In the second part, a personalized network model of the mutual relationships among momentary self-reported pleasure and lifestyle behaviors will be constructed to provide insight into temporal, potentially causal, patterns. In this part, only the lifestyle behaviors that show sufficient variability to be informative will be included. To create the personal networks, we will use Vector Autoregression (VAR) and Autoregressive Moving Average (ARMA) analyses. In the third part, we will compare participant’s average levels of lifestyle behaviors to normal population levels as observed in our own screening data as well as data from previous cohort studies in the same age group (e.g., TRAILS, [50]), in order to provide insight in plausible candidates for lifestyle changes. Based on the information presented in the previous parts, a selection will be made of the two or three lifestyle behaviors that bear the most promise for inducing pleasure, and this will be translated into a personalized lifestyle advice. Each participant will be advised to change at least two and at most three lifestyle behaviors. If possible, the advice will be based on the personalized network model described above, as this provides information about causal relationships between lifestyle behaviors and pleasure that are specific for this person. In case of too few variables in the model (i.e., too little variation in lifestyle variables) or no clear associations with pleasure, we will base the advice on the comparisons with norm levels. The advice will be discussed with the participants in person, based on a written report which participants are allowed to take home.

#### Tandem skydive

A tandem skydive is a skydive from an airplane during which the participant is securely attached to a trained tandem master. The tandem skydives will be performed from airport Hoogeveen at Skydive association Eelde-Hoogeveen. Participants do not need an extensive training; a brief instruction suffices. When they arrive at airport Hoogeveen they will first receive a brief instruction on how to keep their body in the air and how to land. Skydives will be made from an altitude of three kilometres. Landing will be in a sitting position on grass. If it turns out that participants categorically decline the tandem skydive, an alternative thrill experience will be offered. Alternatives are the ‘Skydiver’ or the ‘Goliath’, both attractions in a Dutch amusement park (i.e., Walibi Holland) that offer free fall experiences.

#### No intervention

The group receiving no intervention will continue with the momentary assessments and participate in a short meeting in which progress is checked. We chose to include an active control group that continues with momentary assessments to exclude the possibility that positive effects in the intervention groups are due to the mere registration of emotions and behaviors.

### Materials

#### Screening and monthly questionnaires

An overview of all planned monthly questionnaires can be found in Table 1. The measures in the monthly questionnaires are secondary outcome variables.

**Table 1 Tab1:** Screening and Monthly Questionnaires Used in the Present Study

Concept	Questionnaire	Description	Items	Range	Authors	Assessed at:
Demographics		Questions on sex, birth date, living situation, romantic relationship, education, employment, current and lifetime psychiatric diagnosis, income	20			T0
Exclusion criteria		Questions regarding no possession of smartphone, psychiatric treatment, use of psychotropic medication, adverse conditions for skydive (e.g., epilepsy, cardiovascular problems, weight, height, pregnancy), experience with skydive	16			T0-T6
Reward responsiveness	RR	Questionnaire assessing reward responsiveness	8	1–4	Van den Berg, Franken, & Muris, 2010 [56]	T0-T6
Pleasure and pleasure loss	DDOPS	Questionnaire assessing pleasure in different domains (i.e., perceptual, social, sexual and personal achievement) and different dimensions (i.e., consummatory, anticipatory, motivational)	31 pleasure level items, 31 pleasure change items	1–100 for level of pleasure, 1–5 for change in pleasure	[name] et al., submitted	T0-T6
Lifestyle factors	TRAILS lifestyle	Questionnaire assessing the frequency of and amount of time spent on various lifestyle-related activities in a typical week (e.g., traveling to work, hobbies, leisure activities, exercise).	27 + 3–4 extra items per endorsed activity	Yes/no + frequency + time	Ormel et al., 2012 [57]	T0-T6
Substance use	TRAILS substance use	Questionnaire assessing the frequency and amount of smoking, alcohol, soft drugs and hard drugs.	4–12	Differs per question		T0-T6
Life events and difficulties	TRAILS + own items	Questionnaire assessing chronic difficulties (e.g., long lasting conflict, chronic disease or handicap, unemployment) and recent life events (i.e., relationship break-up, failing to reach important goal, death of loved one).	13	Yes/no	Ormel et al., 2012 [57]	T0-T6
Depressive symptoms	PHQ-9	Questionnaire assessing depressive symptoms in the past two weeks, based on the DSM-IV criteria for depression.	9	0-3	Kroenke, Spitzer, & Williams, 2001 [58]	T0-T6
Psychopathology	ASR	Questionnaire assessing various mental health problems in the past six months.	123	0–2	Achenbach & Rescorla, 2001 [59]	T0, T5, T6
Positive affect	PA	Questionnaire assessing general positive affect, which was partly based on previous research and partly newly constructed.	11		Wichers et al., 2007; Wichers, Lothmann, Simons, Nicolson, & Peeters, 2012 [60, 61]	T0-T6
Effortful control	ATQ-EC	Questionnaire assessing activation control, attentional control and inhibitory control.	19	1–7	Evans & Rothbart, 2007 [62]	T0, T4
Extraversion	BFI-E	The extraversion subscale from the Big Five Inventory.	8	1–5	Denissen, Geenen, van Aken, Gosling, & Potter, 2008 [63]	T0
Self-efficacy	GSS	Questionnaire assessing general self-efficacy.	10	1–4	Teeuw, Schwarzer, & Jerusalem, 1994 [64]	T0-T6
Social comparison	SCS	Questionnaire assessing different aspects of social comparison: judgments with regard to social rank, social attractiveness, and social group fit.	10	1–10	Allan & Gilbert, 1995 [65]	T0-T6
Consummatory and anticipatory pleasure	TEPS	Questionnaire assessing the general level of consummatory (9 items) and anticipatory pleasure (9 items).	18	1–6	Gard, Gard, Kring, & John, 2006 [66]	T0
Facial emotion recognition	FER morphing task	Task consisting of 24 video clips in which a neutral face morphs into a face with an emotional expression of anger, fear, sadness or happiness. Assesses average reaction time (i.e., speed) and number of correctly identified emotions (i.e., accuracy).	24	n/a	Heuer, Lange, Isaac, Rinck, & Becker, 2010 [67]	T0, T2, T3, T4

#### Momentary questionnaires

The items for the momentary questionnaires are presented in Table 2. Pleasure is the primary outcome measure. The other momentary items relate to secondary outcome variables.

**Table 2 Tab2:** Description of Momentary Questionnaire

Question	Dutch	Translation	Response range	Range	Description
1.	Ik probeerde in slaap te vallen om…	I tried to fall asleep at…	Hours - minutes	n/a	Time of trying to sleep
2.	Aantal minuten totdat ik in slaap viel	Number of minutes until falling asleep	Number of minutes	n/a	Time until falling asleep
3.	Ik werd wakker om…	I woke up at…	Hours - minutes	n/a	Time of waking up
4.	Hoeveel keer werd ik wakker gedurende de nacht?	How many times did I wake up during the night?	0, 1, 2, 3, 4, 5 or more	0–5	Frequency of awakenings
5.	Totaal aantal minuten wakker geweest	Total number of minutes awake	Number of minutes		Time of awakenings
6.	Mijn slaapkwaliteit was	My sleep quality was	“Very bad” to “Very good”	0–100	Sleep quality
7.	Ik heb vervelend gedroomd	I had bad dreams	“Not at all” to “Very much”	0–100	Nightmares
8.	Ik voelde me uitgerust bij het wakker worden	I felt rested when I woke up	“Not at all” to “Very much”	0–100	Rest
9.	Ik ben nu…	I am now…	(1) Home (2) Work/school (3) On the way (4) Restaurant/café (5) In nature (6) Vacation home/hotel/camping (7) Hospital/care facility (8) Shop (9) Gym/sports club (10) Somewhere else	1–10	Current location (only one box could be checked)
10.	Ik ben nu…	I am now…	(1) Alone (2) With partner (3) With family (4) With friends (5) With fellow students (6) With colleagues (7) With acquaintances (8) With strangers	1–8	Current social context (multiple answers possible)
11.	Ik voel me nu plezierig	I feel pleasurable	“Not at all” to “Very much”	0–100	Current pleasure
12.	Ik voelde me geïnteresseerd in de dingen om me heen	I felt interested in the things around me	“Not at all” to “Very much”	0–100	Positive affect, low arousal
13.	Ik voelde me overstuur	I felt upset	“Not at all” to “Very much”	0–100	Negative affect, high arousal
14.	Ik voelde me opgewekt	I felt joyful	“Not at all” to “Very much”	0–100	Positive affect, high arousal
15.	Ik voelde me somber	I felt gloomy	“Not at all” to “Very much”	0–100	Negative affect, low arousal
16.	Ik voelde me daadkrachtig	I felt determined	“Not at all” to “Very much”	0–100	Positive affect, high arousal
17.	Ik was niet vooruit te branden	I felt sluggish	“Not at all” to “Very much”	0–100	Negative affect, low arousal
18.	Ik voelde me kalm	I felt calm	“Not at all” to “Very much”	0–100	Positive affect, low arousal
19.	Ik voelde me angstig	I felt anxious	“Not at all” to “Very much”	0–100	Negative affect, high arousal
20.	Ik voelde me levenslustig	I felt lively	“Not at all” to “Very much”	0–100	Positive affect, high arousal
21.	Ik voelde me verveeld	I felt bored	“Not at all” to “Very much”	0–100	Negative affect, low arousal
22.	Ik voelde me enthousiast	I felt enthusiastic	“Not at all” to “Very much”	0–100	Positive affect, high arousal
23.	Ik voelde me geirriteerd	I felt irritated	“Not at all” to “Very much”	0–100	Negative affect, high arousal
24.	Ik voelde me ontspannen	I felt relaxed	“Not at all” to “Very much”	0–100	Positive affect, low arousal
25.	Ik voelde me vrolijk	I felt cheerful	“Not at all” to “Very much”	0–100	Positive affect, high arousal
26.	Ik voelde me nerveus	I felt nervous	“Not at all” to “Very much”	0–100	Negative affect, high arousal
27.	Ik voelde me tevreden	I felt content	“Not at all” to “Very much”	0–100	Positive affect, low arousal
28.	Ik voelde me lusteloos	I felt listless	“Not at all” to “Very much”	0–100	Negative affect, low arousal
29.	Ik voelde me energiek	I felt energetic	“Not at all” to “Very much”	0–100	Positive affect, high arousal
30.	Ik heb sinds de laatste meting plezier gehad	I experienced pleasure since the last assessment	“Not at all” to “Very much”	0–100	Pleasure since the last assessment
31.	Ik heb gepiekerd	I have been worrying	“Not at all” to “Very much”	0–100	Worrying
32.	Ik was tevreden over mezelf	I was pleased with myself	“Not at all” to “Very much”	0–100	Self-esteem
33.	Waar was ik sinds de vorige meting?	Where was I since the last assessment?	(1) Home (2) Work/school (3) On the way (4) Restaurant/café (5) In nature (6) Vacation home/hotel/camping (7) Hospital/care facility (8) Shop (9) Gym/sports club (10) Somewhere else	1–10	Location since last assessment (multiple answers possible). In case of multiple locations, go to 34.
34.	Waar heb ik de meeste tijd doorgebracht?	Where have I spent most time?	Only locations checked in previous question		Main location (only one answer possible).
35.	Ik ben sinds de laatste meting buiten geweest	I have been outside since the last assessment	“Not at all” to “Very much”	0–100	Being outside
36.	Ik was sinds de laatste meting	Since the last assessment, I was	(1) Alone (2) With partner (3) With family (4) With friends (5) With fellow students (6) With colleagues (7) With acquaintances (8) With strangers	1–8	Social context since last assessment (multiple answers possible). All checked answers were included in next question
36. a-x	Tijd die ik met [gezelschap uit vraag 36] heb doorgebracht	Time spent with [company from question 36]	“Very little” to “Very much”	0–100	Time spent in social context
37.	Hoeveel heb ik gepraat met andere mensen?	How much have I been talking to other people?	“Not at all” to “Very much”	0–100	Social interaction
38.	Ik heb sinds de laatste meting de volgende activiteiten gedaan:	I participated in the following activities since the last assessment:	(1) Watching TV (2) Listening to music (3) Studying (4) Reading a book or magazine (5) Shopping (6) Using the internet (7) Gaming (8) Working (9) Having sex (alone or with someone else) (10) Household chores (11) Sports (12) Going to a bar or club (13) Going out for dinner (14) Going to the movies, theatre, museum or concert (15) Sleeping (16) Using social media (17) Hobbies (18) Other, namely….	1–18	Activities (multiple answers possible)
39.	Ik ben sinds de laatste meting lichamelijk actief geweest	I have been physically active since the last assessment	“Not at all” to “Very much”	0–100	
40.	Ik heb sinds de laatste meting de volgende middelen gebruikt:	I used the following substances since the last assessment:	(1) Nothing (2) Caffeine (3) Nicotine (4) Medication (5) Alcohol (6) Cannabis (7) Stimulants (8) Sedatives (9) Other drugs	1–9	Substance use (if caffeine, nicotine, or alcohol was checked, go to question 41)
41.	Aantal [cafeine-houdende drankjes/sigaretten/glazen alcohol] dat ik sinds de laatste meting heb [gedronken/gerookt/gedronken]	Number of [caffeine-containing drinks/cigarettes/glasses of alcohol] consumed since the last assessment	Number	n/a	Amount of substance use
42.	Ik heb sinds de laatste meting het volgende gegeten:	I have eaten the following since the last assessment:	(1) Nothing (2) Dairy products (3) Vegetables/fruit (4) Bread/pasta/rice/potatoes (5) Meat (6) Fish (7) Eggs (8) Nuts (9) Meat or dairy substitutes	1–9	Food intake
43.	Hoeveel zoete snacks (bijv. koek, snoep) heb ik gegeten?	How many sweet snacks (e.g., cookies, sweets) did I eat?	“Nothing” to “A lot”	0–100	Sweet snacks
44.	Hoeveel hartige snacks (bijv. patat, chips) heb ik gegeten?	How many savory snacks (e.g., French fries, potato chips) did I eat?	“Nothing” to “A lot”	0–100	Savory snacks
45.	Denk aan de leukste gebeurtenis die je hebt meegemaakt sinds de laatste meting: hoe plezierig was deze gebeurtenis voor jou?	Think about the most pleasant event you experienced since the last assessment: how enjoyable was this experience?	“Not at all” to “Very much”	0–100	Pleasantness most positive event
46.	Denk aan de leukste gebeurtenis die je hebt meegemaakt sinds de laatste meting: hoe belangrijk was deze gebeurtenis voor jou?	Think about the most pleasant event you experienced since the last assessment: how important was this experience?	“Not at all” to “Very much”	0–100	Importance most positive event
47.	Denk aan de vervelendste gebeurtenis die je hebt meegemaakt sinds de laatste meting: hoe onplezierig was deze gebeurtenis voor jou?	Think about the most unpleasant event you experienced since the last assessment: how unpleasant was this event?	“Not at all” to “Very much”	0–100	Unpleasantness most negative event
48.	Denk aan de vervelendste gebeurtenis die je hebt meegemaakt sinds de laatste meting: hoe belangrijk was deze gebeurtenis voor jou?	Think about the most unpleasant event you experienced since the last assessment: how important was this event?	“Not at all” to “Very much”	0–100	Importance most negative event
49.	Ik heb sinds de laatste meting lichamelijk ongemak ervaren (hoofdpijn, diarree, zware benen, etc.)	I have experienced physical discomfort since the last assessments (head ache, diarrhea, heavy legs, etc.)	“Not at all” to “Very much”	0–100	Physical discomfort
50.	Sinds de laatste meting had ik het:	How busy was I since the last assessment:	(1) Much too busy (2) Too busy (3) Pleasantly busy (4) Neutral (5) Pleasantly quiet (6) Too quiet (7) Much too quiet	1–7	Time pressure/stress

*Note.* The affect items (i.e., item 12–29) were assessed about the current moment in the morning assessment, and about the time since the last assessment in the afternoon and evening assessments. These items are based on Russell’s circumplex model of affect [68], including items for high and low arousal PA and NA, and we created some additional items to measure pleasure (items 11, 30), interest (item 12), and motivation (items 16, 17, 28). The sleep items (items 1–8) were based on the Pittsburgh sleep diary [69]. Items for location (items 9, 33), social context (items 10, 36, 36a-x), worrying (item 31), self-esteem (item 32), being outside (item 35), social interaction (item 37), activities (item 38), physical activity (item 39), positive and negative events (items 45–48), physical discomfort (item 49), and time pressure (item 50) were adapted from previous ESM studies [55, 70–73]. We created new items to assess substance use (items 40–41), food intake (item 42), and sweet and savory snacks (items 43, 44)

#### Blood samples

The collected blood samples will be used to measure levels of dopamine, serotonin, oxytocin, adrenalin, noradrenalin, and brain-derived neurotrophic factor (BDNF). Part of the first blood sample will be stored to allow later assessment of polymorphisms in relevant candidate genes; and part of the first, third, fifth and sixth blood sample will be stored to allow later epigenetic analyses. As mentioned in the introduction, (epi-) genetic factors are assumed to play an essential role in mechanisms explaining why interventions are or are not effective in reducing symptoms. We will examine genetic polymorphisms in several genes (i.e., DRD2, DRD4, DAT, COMT, 5-HTTLPR, BDNF). Further, we will examine epigenetic modifications in genes in the dopaminergic system and in the BDNF gene. Given the relatively small sample size, power to detect (epi-) genetic effects is probably insufficient with the current (epi-) genetic analyses techniques. However, analytic techniques improve rapidly, allowing smaller sample sizes. We will only conduct these (epi-) genetic analyses when the appropriate techniques and analyses are available, and the statistical power is sufficient to allow meaningful conclusions. At each of the time points, the blood samples will consist of one 10 ml EDTA K2E tube and, dependent on time point, one or two 4 ml EDTA K2E tube(s).

#### Saliva samples

We will assess the biomarker alpha-amylase in saliva around the skydive, to examine acute mechanisms of change [20, 37].

### Sample size calculation

The sample size of the survey will be at least *N* = 2000. Estimates from a pilot study conducted in 277 young adults, using the same criteria as will be used in the present study, showed that around 5 % of the sample experienced persistent anhedonia. Hence, a sample size of 2000 will yield *N* = 100 individuals with persistent anhedonia, which will warrant sufficient power to investigate relationships among different dimensions and domains of anhedonia and between these dimensions and domains and other relevant factors.

In the intervention study, we aim to collect time series data in at least 60 (72 including oversampling) anhedonic persons. With regard to our main research question, that is, whether the different interventions lead to improvements in pleasure scores, we will follow two approaches. First, following from the exploratory nature of the intervention study, we will examine each individual series of observations to assess individual response patterns. This will be done by means of (interrupted) times series analysis (ITS) to detect time trends in the amount of pleasure experienced during the study, and differences in the level and slope between pre- and post- intervention pleasure levels. It is not well possible to calculate the power of time series analyses because that depends on a wide range of factors, but a general recommendation is that there should be at least 12 observations before and 12 after the intervention [51]. Considering that we have at least 90 observations before and after the interventions, we do not foresee any power problems.

To explore patterns of change at a group level, we will conduct multilevel analyses with pleasure level after the intervention as outcome variable. In these analyses, Level 1 represents the assessment level (i.e., momentary assessments within individuals) and Level 2 the individual level. In order to be able to examine cross-level interactions (i.e., testing whether Level 1 relations differ between individuals), a minimum number of 50 Level 2 cases and 20 Level 1 cases should be sufficient [52]. As we include at least 60 individuals (Level 2) and 90 momentary assessments (Level 1), we should have sufficient power to answer our main research question.

Finally, to explore patterns of change in monthly assessed questionnaires, we will use repeated measures ANOVAs. A power analyses in Stata showed that we need 21 individuals per group to detect a large difference between groups (Cohen’s d = 0.8) with a correlation of 0.6 between the repeated assessments (power = 0.8, alpha = 0.05). As we include 24 participants per group (oversampled for drop-out), we should have enough power to detect large differences.

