## Methods

### Participants

For the screening survey, 2000 young adults (18–24 years old) will be recruited from the general population. Inclusion criteria for the survey are age between 18–24 years and sufficient knowledge of the Dutch language. Inclusion criteria for the anhedonia group are (a) persistent pleasure loss and (b) willingness to perform a skydive. For the non-anhedonic control group, the inclusion criteria are (a) no loss of pleasure and (b) willingness to perform a skydive. Exclusion criteria are inability to keep an electronic diary three times a day; current professional treatment for psychiatric problems; current use of psychotropic medication; epilepsy; pregnancy; conditions that make it impossible to be attached to the tandem master (e.g., loose prostheses); height of more than 2 m; weight of more than 95 kg; inability to raise one’s legs 90° (needed for safe landing after tandem skydive); significant visual or hearing impairments; experience with skydiving, bungee jumping, base jumping, or skyjumping; cardiovascular complaints/problems. All criteria were included as questions in the screening survey.

We will use three questions from the Domains and Dimensions of Pleasure Scale ​(DDOPS; [name], [name], [name], [name], [name], & [name]: Domains and Dimensions of Pleasure Scale (DDOPS): a novel questionnaire to assess anhedonia, submitted) to measure persistent loss of pleasure. These questions assess the level of pleasure experienced during the past two weeks, whether this level represents a loss compared to what is considered normal to that person, and the duration of the loss. Participants who report low pleasure levels (score below the 25th percentile), a loss compared to normally experienced pleasure levels, and a minimum duration of the loss of 2 months are eligible for inclusion. We aim to complete the data collection in at least 60 anhedonic persons (20 in each condition). Because we expect some dropout during the data collection, we decided to select 24 individuals for each condition (72 in total). The non-anhedonic control group will consist of 60 individuals.

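### The questionnaire power claim sets its required 21 per group against the 24 enrolled rather than the 20 completers targeted, and the planned repeated measures ANOVA leaves the pre-intervention score unadjusted

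*Protocol article*

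**What the plan says.** In the Protocol article, the end of *Sample size calculation* covers the monthly questionnaires: "to explore patterns of change in monthly assessed questionnaires, we will use repeated measures ANOVAs". The size follows: "A power analyses in Stata showed that we need 21 individuals per group", "to detect a large difference between groups (Cohen’s d = 0.8") and "with a correlation of 0.6 between the repeated assessments" ("power = 0.8, alpha = 0.05"). The section then concludes: "As we include 24 participants per group (oversampled for drop-out), we should have enough power to detect large differences".

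*Participants* gives a different number for those expected to finish: "We aim to complete the data collection in at least 60 anhedonic persons (20 in each condition"). The 24 per condition are selected because some dropout is expected.

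*Procedure* has anhedonic participants complete the questionnaire before and after each month, with randomisation after the first month. Two scores therefore precede randomisation (start and end of month 1), and one at the end of month 2 follows the randomised period. From the start of month 3 all participants choose freely among the options.

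*Primary outcome variables* compares post-intervention momentary pleasure between arms while controlling for its pre-intervention level. No such control is stated for the questionnaires, which *Screening and monthly questionnaires* classes as secondary outcomes.

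**The concern.** There are two connected issues. First, the required number is set against the wrong count. The 24 include a reserve for losses, so the adequacy of 21 should be judged against the number expected to be analysed. The stated minimum, 20, is one below the requirement.

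Second, a repeated measures ANOVA on pre and post scores tests the group effect as a change or interaction. With a correlation of 0.6, that uses the pre-intervention score less efficiently than adjusting for it. With about 20 per arm, and power claimed for large effects alone, precision available from data already in hand matters. What is at stake is the precision of the secondary comparisons and the accuracy of one power statement. The validity of the trial is not in question.

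**Working it through.** **Inputs.** From *Sample size calculation*: d = 0.8 (SD set to 1), r = 0.6, power 0.80, alpha 0.05, 21 required per group, 24 enrolled per group. From *Participants*: at least 20 completers per condition. Assumed because not stated: two-sided alpha, one pairwise comparison of two arms, and, for steps 1 to 3, one pre and one post score. Power is from the noncentral t distribution with noncentrality (0.8/√v)·√(n/2), where v is the variance factor.

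**1. Reproducing 21.** A pre-to-post change has v = 2(1 − r) = 2(0.4) = 0.80. The mean of two assessments has v = (1 + r)/2 = 1.6/2 = 0.80, so both give the same size.
- Normal approximation: n = 2(1.960 + 0.842)² × 0.80/0.64 = 19.6, so 20.
- t-test: 21 per group (power 0.807). The stated figure is reproduced.
- A one-sided t-test on the post score alone also gives 21, but it makes no use of the correlation. The figure 21 therefore does not identify the test.

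**2. Power at the document's own counts, v = 0.80 (t-test).**

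| n per group | Power |
|---|---|
| 20 (minimum completers) | 0.787 |
| 21 (stated requirement) | 0.807 |
| 24 (enrolled) | 0.858 |

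At 20 the shortfall from 0.80 is 1.3 points.

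**3. Adjusting for one pre-intervention score.** v = 1 − r² = 1 − 0.36 = 0.64, which is 20% below 0.80.
- Normal approximation: 15.7, so 16.
- t-test: 17 per group (power 0.807; 0.806 with one degree of freedom spent on the covariate).
- Power at 20 per group: 0.869 (0.868 with that degree of freedom spent).

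**4. Using both pre-randomisation scores, all correlations 0.6.** The mean of the two has variance 0.80 and covariance 0.6 with the post score.
- Post minus that mean: v = 1 + 0.80 − 2(0.6) = 0.60. Power at 20 is 0.889, and 16 per group are needed.
- ANCOVA on that mean: v = 1 − 0.36/0.80 = 0.55. Power at 20 is about 0.91.
- Three-wave ANOVA, group-by-time test on 2 degrees of freedom, two arms, effect at the last wave alone: power at 20 is 0.825, and 19 per group suffice (0.804).

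Step 4 shows that the shortfall in step 2 depends on the number of waves and the test. It also shows that adjustment beats the matching change contrast with two pre-scores (0.55 against 0.60), as it does with one (0.64 against 0.80).

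**The case against.** The strongest reply is that no power failure is established. The article does not give the number of waves or the effect tested. With three waves the group-by-time test has 82.5% power at 20 per group, and contrasting the post score with the mean of both pre-scores has 88.9%. Even on two waves the gap is 1.3 points; by normal approximation 20 suffice, and 20 is worded as a minimum. The outcomes are secondary in a study described as exploratory. Under randomisation a change comparison is valid, and an article may leave covariates to a fuller document. All of this stands, and it limits the first issue to a mismatched comparison of counts. It does not remove the efficiency gain, which holds with one or two pre-scores.

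Three stronger readings are tempting and should not be drawn:
- That the stated 80% is definitely missed. That follows on the two-wave t-test reading but not on others equally open.
- That the treatment effect would be read from a group main effect averaged over baseline, which would dilute an effect present after the intervention alone. The stated aim of exploring patterns of change points to group-by-time instead.
- That a one-in-six loss (4 of 24) is planned. The article expects some dropout and gives no rate; that fraction is back-calculated from the minimum, so probabilities of retaining 21 per arm built on it describe a worst planned case.

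**Conclusion.** The point holds in limited form. The article judges 21 per group against 24 enrolled, although its own minimum for completers is 20. On the two-wave, two-sided t-test reading that reproduces 21, power at 20 is about 79%, a marginal shortfall that disappears under other readings the text allows.

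The more useful conclusion is that adjusting for the pre-intervention score gives about 87% at 20 completers (17 per group needed), or about 91% with the mean of both pre-randomisation scores. This rests on r = 0.6 applying between pre and post scores (and between all pairs of waves for the 91%), d = 0.8, two-sided alpha 0.05 and one pairwise comparison. It is a worthwhile improvement to a secondary analysis and a correction to one sentence. It does not show that the planned ANOVA is invalid.

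**What to change.** For the randomised comparison, analyse each end-of-month-2 questionnaire score by ANCOVA or an equivalent mixed model. Include assigned arm, pre-intervention score (end of month 1, or the mean of the two pre-randomisation scores, chosen in advance) and sex, the randomisation stratum. Keep any multi-wave description of patterns of change as exploratory.

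Replace the sentence relying on 24 per group with power at 20 completers per group, for one pairwise comparison at two-sided alpha 0.05, d = 0.8 and r = 0.6: about 87% with one pre-score (17 per group needed), or about 91% with the mean of two if all correlations are 0.6. If repeated measures ANOVA is kept as the main test, state the waves, the effect tested and the sidedness behind the 21, and compare that number with completers.

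The cost is wording and a restated figure. No further data or participants are needed, and the change brings the questionnaires into line with the adjustment already planned for momentary pleasure.
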